## Abstract

Despite the importance of knowing the cognitive capabilities of children with neurodevelopmental conditions, less than one-third of children with cerebral palsy participate in standardized assessments. Globally, approximately 50% of people with cerebral palsy have an intellectual disability and there is significant risk for domain-specific cognitive impairments for the majority of people with cerebral palsy. However, standardized cognitive assessment tools are not accessible to many children with cerebral palsy, as they require manual manipulation of objects, verbal response and/or speeded response. As such, standardised assessment may result in an underestimation of abilities for children with significant motor and/or speech impairment. The overall aim of the project is to examine and compare the psychometric properties of standardised cognitive assessment tools that have been accommodated for use with either a switch device or eye-gaze control technologies, with the specific aims to: (1) Examine the psychometric properties (measurement agreement and validity) of accommodated assessment tools by comparing the performance of typically developing children on six cognitive assessment tools administered *via* standardised versus accommodated (switch or eye-gaze control) administration; (2) Describe and compare the performance and user experience of children with cerebral palsy on six accommodated cognitive assessments administered *via* switch or eye-gaze control technologies. Secondary aims are to: (1) Describe the completion rates and time to complete assessments of participants in each group; (2) Within the group with cerebral palsy, examine the effects of condition-specific characteristics (type of cerebral palsy, functional levels, and pain) and demographics (age, socio-demographic) on participation. This protocol paper describes a two-phase validation and acceptability study that utilizes a mixed-model design. This study will collect concurrent data from 80 typically developing children and 40 children with cerebral palsy, who use switch or eye-gaze control technology as alternate access communication methods. The set of instruments will measure receptive vocabulary, fluid reasoning, sustained attention, vision perception, visuospatial working memory and executive functions. Data analyses will be conducted using SPSS v. 25 and R v 4.1.0. SPSS Sample Power 3 was used for power computation and allows for a 10% drop out rate. Quantitative descriptive statistics, measurement agreement data plotting, bivariate and multiple regressions analysis will be conducted using appropriate methods.

## Introduction

Cerebral palsy is primarily a motor disorder that entails significant risk for a range of associated impairments including behavioural difficulties, intellectual disability, and hearing, vision, and speech impairments (Rosenbaum et al., 2007). A systematic review of available international population-based data found that one in three children with cerebral palsy have a severe gross motor impairment, one in four cannot talk, one in two have an intellectual disability and one in four have a behaviour disorder (Novak et al., 2012). A population based Swedish study reported that one in two children with cerebral palsy have a speech disorder (Nordberg et al., 2013). The speech and motor difficulties associated with cerebral palsy may mask recognition of a child’s cognitive capabilities, in part due to presumptions of low capability associated with physical disability. Findings show that severity of motor impairment of children with spastic cerebral palsy correlate with severity of cognitive impairment. In contrast, for children with dyskinetic cerebral palsy, severe motor impairment and reduced language skills due to dysarthria can result in an underestimation of the child’s cognitive abilities (Fennell and Dikel, 2001). These presumptions of lower capacity may restrict access to opportunities for learning and development, as family, peers, educators and health professionals fail to recognise and respond to the child’s intrinsic developmental potential (Ashwal et al., 2004; Blair, 2016). Therefore, early detection of cognitive capability and implementation of necessary interventions are essential to optimizing the development, growth and quality of life of children with cerebral palsy; enabling them to reach their full potential (Ashwal et al., 2004; Warschausky et al., 2012). Despite the importance of knowing a child’s level of cognitive functioning, less than one-third of children with cerebral palsy have standardized assessments (Andersen et al., 2008; Sigurdardottir et al., 2008; Romeo et al., 2011; Sherwell et al., 2014; Stadskleiv et al., 2015).Currently, standardised cognitive assessment tools remain inaccessible to children cerebral palsy with significant motor and speech impairments. The most commonly used intelligence tests require quick manual manipulation of objects and/or verbal responses, which are scored according to the speed at which they are performed (Coceski et al., 2021). As such, normed comparisons of cognitive measures for children with significant motor and/or speech impairment are unlikely to yield valid estimates of cognitive capacity, particularly for children who are unable to manipulate objects and/or use assistive technology to access computers and communication devices (Miller and Rosenfeld, 1952; Hohman, 1953).

Assistive technologies can bridge the gap between physical impairments and task requirements for children with cerebral palsy who have significant motor and speech impairments (Murchland and Parkyn, 2010). Assistive technologies for communication include low-tech devices, such as picture boards and exchange systems, and high-tech devices, such as computers or electronic devices which produce synthetic or digitalised speech (Bailey et al., 2006). Mechanical switches and eye-gaze control technology are commonly used to access these high-tech devices, replacing the need to use a computer keyboard or mouse. Mechanical switches can enable the child to serially scan response options on a screen (i.e., multiple-choice scanning). Similarly, by enabling a child to control the cursor with their eyes, eye-gaze technology allows the user to make a selection onscreen by sustaining gaze on a desired response option (i.e., point and click approach). Therefore, undertaking cognitive assessment using these common communication access methods should provide more accurate information regarding a child’s cognitive capabilities, as they bypass sophisticated motor and speech requirements (Karlsson et al., 2022). Conversely, the introduction of assistive technology management may involve cognitive demands or mental workloads which are not specific to the construct of assessment interest and may prove a liability.

Enthusiasm for accessible accommodations is tempered by evidence that modifying standardized procedures to make them accessible may change the psychometric properties of tests (Hill-Briggs et al., 2007; Warschausky et al., 2012). Therefore, the Standards for Psychological and Educational Testing (American Educational Research Association (AERA), 2014) include recommendations to demonstrate comparability by pilot testing accommodations prior to clinical use and providing psychometric data regarding test validity. A systematic approach can include first examining the effects of accommodations on the psychometric properties in a sample of children who do not have significant impairments and can participate in the standard and modified versions of tests. Following demonstration of measurement agreement in a typically developing sample, subsequent research can examine the psychometric effects of accommodations in the target population.

Research has shown that it is possible to make accommodations to testing administration procedures of language assessments without negatively impacting test fidelity (Kurmanaviciute and Stadskleiv, 2017). A study by Warschausky et al. (2012) found that assessment tools with 4-item forced choice responses, such as the Peabody Picture Vocabulary Test (PPVT-III) and the Peabody Individual Achievement Test–Revised Reading Comprehension could be administered *via* switch and head mouse assistive technologies, without significantly altering the psychometric properties of the assessment tool (Warschausky et al., 2012). Event Related Potential (ERP), and other uses of electroencephalogram (EEG), is novel accommodations explored in the literature as alternate response formats and access methods for cognitive assessment for children and adults with impaired speech or fine motor skills (Alcaide-Aguirre et al., 2017; Berchio and Micali, 2022). While these studies show promise, translation of ERPs into clinical practice poses challenges, with the technology not fully ready for commercial use, and as such implementation does not appear imminent. Furthermore, the use of EEG for cognitive assessment will require significant training of qualified psychologists and allied health professionals, or development of a new work force skilled in basic cognitive assessment and ERP-facilitated testing.

Researchers have also investigated non-standardised response modalities such as finger pointing, eye-gaze and partner assisted scanning, as accommodations to increase accessibility of assessment measures (Kurmanaviciute and Stadskleiv, 2017; Fiske et al., 2020). For example, in a sample of 27 typically developing children aged 5 to 6 years old, Kurmanaviciute and Stadskleiv (2017) assessed the impact of altered response modality on measures of verbal comprehension and non-verbal reasoning. Results demonstrated that response modality did not impact performance, though partner assisted scanning was more time-consuming.

Similarly, young children’s performance on the Computer-Based Instrument for Low motor Language Testing (C-BiLLT), a test developed to assess spoken language comprehension in unintelligible or non-speaking children with motoric impairment (Geytenbeek et al., 2014), was found to be equally reliable regardless of whether eye-gaze pointing or finger pointing was used (Stadskleiv, 2020). This access method has been successfully used in a number of key research studies to date (Stadskleiv et al., 2017, 2018).

Thus, studies have demonstrated the feasibility of making accommodations to language assessments, enabling reliable assessment of receptive vocabulary. However, there is a paucity of reliable assessment tools for other domains of cognitive functioning for children with fine motor and/or speech impairments. Hence, the primary aim of this project is to examine and compare the psychometric properties of six domain specific cognitive assessment tools (receptive vocabulary, fluid reasoning, sustained attention, strategic planning, working memory, and visual perception) accommodated for use with assistive technology.

### Primary aims and hypotheses

Aim 1. Examine the psychometric properties (measurement agreement and validity) of accommodated assessment tools by comparing the performance of typically developing children on six cognitive assessment tools administered *via* standardised versus accommodated (switch or eye-gaze control) administration.

*Hypothesis 1-1*: The two types of accommodated instruments (switch or eye-gaze control) will yield standard scores that are not statistically significantly different from standardized administration counterparts.

*Hypothesis 1-2*: Accommodated instruments will demonstrate intraclass correlation indexes of agreement with standard counterparts that would be at least 0.75 (Lee et al., 1989).

*Hypothesis 1-3*: Bland Altman plots will provide further evidence of measurement agreement and test bias, with *a priori* criteria of an acceptable upper 95% confidence limit and lower 95% confidence limit of 1.96 SD of the differences between the methods as equal to or smaller than the normative standard deviation (SD = 15; Bland and Altman, 1986).

Aim 2. Describe and compare the performance and user experience of children with cerebral palsy on six accommodated cognitive assessments administered *via* switch or eye-gaze control technologies.

*Hypothesis 2-1*: Group differences (typically developing, cerebral palsy) in the nomothetic span of test scores computed as within-group bivariate correlation matrices, will not be statistically significant.

*Hypothesis 2-2*: Within the group with cerebral palsy, the access method (switch, eye-gaze) will not result in significant differences in the nomothetic spans of test scores.

*Hypothesis 2-3*: Within the group with cerebral palsy, access method (switch, eye-gaze) will not have a significant effect on user experience as indicated by personal ratings of task difficulty and satisfaction.

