The *Tower of Hanoi* (*TOH*) will be used to assess executive functions such as problem solving, planning, set shifting and mental flexibility. Traditionally developed for adult populations with neurological impairment, the TOH has since been accommodated as a measure of executive functioning for both children and infants (Welsh et al., 1991; Klahr and Robinson. 1981). In the task, the participant is shown 2, 3 and 4 disc puzzles on 3 rods. Participants are required to re-arrange the disks so that their 3 rods look identical to the examiner’s target rods, following a set of rules and completing the task in as few moves as possible (Welsh et al., 1991). The psychometric properties of the TOH have been examined extensively, with various target displays and scoring rubrics reported. Whilst reported psychometric properties vary considerably across studies (Bishop et al., 2001), it is generally considered an acceptable measure of executive functioning for children (Bull et al., 2004; Anderson et al., 2010).

The *Self-Ordered Point Task* (*SOPT*), developed by Petrides and Milner (1982) will be used to assess visuospatial working memory. Here, participants are shown sets of 6, 8, 10 and 12 abstract images (Strauss et al., 2006). The same images are shown over as many pages as there are images in the set, but the images change location on each page. Participants are instructed to touch a different picture on each page. There are 3 trials for each set, increasing cognitive load as participants are required to recall which pictures have been touched on each trial. Whilst a less commonly used measure of working memory, this is one of the few working memory tasks with psychometric evidence to support its use (Ross et al., 2007), which can be accommodated for eye-gaze and switch access technologies.; results are not time dependent.

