### Data processing and analysis

Data analysis will be conducted using SPSS v. 25 (Statistical Package Social Science, S.F.W, 2018) and R v 4.1.0 (R Core Team, 2021). Raw scores on standardised assessment tools will be converted to scaled scores and/or standard scores where appropriate. Raw scores on the TOH and SOPT will be converted to z-scores using available published data. Descriptive statistics will be used to summarise demographic and clinical characteristics, assessment tool performance, secondary outcomes, and user experience. Prior to undertaking any statistical analysis, the normality of the scaled/standardised scores and Z-scores for the six assessments tool will be assessed overall and for each combination of administration and access method (i.e., standard administration and switch; standard administration and eye gaze control technology; person with cerebral palsy using switch; and person with cerebral palsy using eye-gaze control technology) using Shapiro-Wilks assessment and visual inspection of histograms.

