The measurement agreement and validity of the accommodated assessment tools will be investigated by testing hypotheses of equivalence between scores from the standard administration and scores from the accommodated administration of the assessments. These hypotheses will be tested using paired t-tests for Wilcoxon signed-rank tests if the data is not normally distributed. The significance level for these tests will be adjusted to account for multiplicity and control the overall Type I error rate at 5%. Correlations will be investigated between performances on each of the six assessments for all combinations of access methods, and intraclass correlation coefficients (ICC) will be calculated. For the sample of children without cerebral palsy, the sample size will be sufficient to examine Bland Altman plots for further evidence of measurement agreement and test bias. In addition, we will compare the bivariate correlation matrices with adaptive test scores to examine the nomothetic spans of instruments by comparing coefficients using Fisher’s r to z transformations. Regression models will be investigated to examine between group differences in (i) children with cerebral palsy using switch and eye-gaze control technologies for each of the six assessment tools and for the two user experience measures, and (ii) between typically developing children’s and children with cerebral palsy’s performance using switch and eye-gaze control technologies, across all six assessment tools. Potential confounders and effect modifiers will be investigated for these regression models Associations between test results and secondary outcomes for the children with cerebral palsy will be investigated using chi-squared or Fisher’s exact tests.

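### The Bland-Altman limit of 15 in Hypothesis 1-3 tests nothing for the two tools analysed as z-scores (Tower of Hanoi and Self-Ordered Point Task)

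*Protocol article*

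**What the plan says.** Aim 1 is about "comparing the performance of typically developing children on six cognitive assessment tools administered" in the standard and the accommodated way, so its hypotheses cover all six tools. Hypothesis 1-3 gives the Bland-Altman criterion in advance, with one number: "1.96 SD of the differences between the methods as equal to or smaller than the normative standard deviation (SD = 15"). It exempts no tool and gives no second value for another scale.

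The section 'Data processing and analysis' then fixes the scales. For two tools: "Raw scores on the TOH and SOPT will be converted to z-scores using available published data". For the rest: "Raw scores on standardised assessment tools will be converted to scaled scores and/or standard scores where appropriate". The scales stay side by side in the next step, where "the normality of the scaled/standardised scores and Z-scores for the six assessments tool will be assessed". The Bland-Altman analysis is taken up again in that section ("For the sample of children without cerebral palsy, the sample size will be sufficient to examine Bland Altman plots") without a limit specific to each scale. No section converts z-scores or scaled scores to a metric with SD 15.

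Hypothesis 1-2 is a separate agreement criterion: "intraclass correlation indexes of agreement with standard counterparts that would be at least 0.75".

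**The concern.** A Bland-Altman limit is in the units of the score that is plotted. The value 15 is one normative SD only on a metric whose normative SD is 15. On z-scores one normative SD is 1, so the same printed number is fifteen times as lenient in relative terms.

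Hypothesis 1-3 is the only Aim 1 criterion that bounds, in score units, how far an individual child's two results may lie apart. If it passes whatever the data show, a later report could list TOH and SOPT as meeting a limit set in advance that never tested them.

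**Working it through.** **Inputs**
- Limit L = 15 for 1.96 × SD of the differences (Hypothesis 1-3). It is a chosen constant, so there is no derivation to reproduce.
- TOH and SOPT are z-scores ('Data processing and analysis'); their reference SD is 1 by definition.
- SD of scaled scores: not given. It is treated below as an unknown, s.
- Sample: 80 typically developing children ('Sample size calculations').

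**Formula.** With equal SDs s under both administrations and correlation r between them:
- SD of differences = s × √(2(1 − r))
- half-width = 1.96 × s × √(2(1 − r))

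**What L = 15 allows.** The largest passing SD of differences is 15 / 1.96 = 7.65.

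| Metric | 7.65 in units of s | Half-width at r = 0 | Half-width at r = −1 | Result against 15 |
|---|---|---|---|---|
| Standard score, s = 15 | 0.51 | 41.6 | 58.8 | Both fail |
| z-score, s = 1 | 7.65 | 2.77 | 3.92 | Both pass |

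On the SD-15 metric the limit is demanding. It needs r ≥ 1 − 0.5102² / 2 = 0.870; at r = 0.75 the half-width is 20.8, a fail. On z-scores even perfectly opposed results pass.

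**Sampling check.** In 20,000 simulated samples of 80 children with r = 0, the pass rate was 100% for s = 1 and 0% for s = 15.

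**Stricter reading of the criterion.** Suppose that the mean difference and a 95% confidence bound around the limit of agreement must also fit inside 15. Take r = 0, a bias of 1.25 SD (the acceptable difference named in the sample-size section), and 40 children (an equal split by access method, assumed). The outer bound for z-scores is then 4.8, still far inside 15.

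**If the z-scores in this sample do not have SD 1.** Unrelated scores fail only if s exceeds 15 / (1.96 × √2) = 15 / 2.772 = 5.41 reference SDs.

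**Scaled scores, as a range.** By the same arithmetic, unrelated scores pass on any metric with s ≤ 5.41, and no correlation at all can fail if s ≤ 15 / 3.92 = 3.83. For example, an assumed s = 3 gives 8.32 at r = 0 and 11.76 at r = −1, both passes.

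**With the limit at one normative SD of each metric.** The requirement is the same for every tool: SD of differences ≤ 0.51 s, or r ≥ 0.870 with equal SDs. Unrelated z-scores (2.77 against 1.0) then fail.

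**The case against.** The best defence is that the rule is relative: the yardstick is the normative SD, and 15 is only its value on the standard-score metric. Hypothesis 1-1 speaks of standard scores, and the sample-size section states its margins in SD units (1.25 and 0.4). On that reading the limit for z-scores is already 1.0. This may well be the intent. But the text attaches the value 15 without qualification, and the scoring section names z-scores for TOH and SOPT. A criterion set in advance should not need reinterpretation once the data are in.

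A second defence is that a condensed article leaves scoring detail to the full protocol or analysis plan. That would answer a charge of omission. Here the article prints a number that does not fit its own scoring section.

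The third defence stands and limits the point. The article presents the Bland-Altman analysis as supplementary evidence. The intraclass correlation threshold of 0.75 does not depend on scale, and the unrelated scores in the example above would fail it.

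Three stronger inferences are not supported:
- *That TOH and SOPT would be declared in agreement whatever the data show.* The intraclass criterion prevents this.
- *That four of the six tools are affected.* The article does not assign scaled scores to particular tools or give their SD, so only two are certain.
- *That the z-scores rest on mismatched published data.* The remark "with various target displays and scoring rubrics reported" describes the TOH literature only. It does not identify the data used for conversion and says nothing about SOPT. It gives no ground for replacing the normative yardstick with this study's own SD.

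**Conclusion.** The point holds for TOH and SOPT. As printed, the limit tolerates an SD of differences of up to 7.65 reference SDs on z-scores, against 0.51 SD on standard scores. Unrelated z-scores pass with a half-width of 2.77, so for executive function and visuospatial working memory the criterion carries no information.

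This is a practical rather than a mathematical certainty. It assumes that the SD of the z-scores in this sample is somewhere near the reference value of 1, with a wide margin (up to 5.41 if the two administrations are unrelated). For the other four tools the defect is conditional on a scaled score with a small SD being used.

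The consequence is one empty supporting criterion under a primary aim. The intraclass correlation criterion and the sample size, whose margins are in SD units, are unaffected.

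**What to change.** Reword Hypothesis 1-3 so that the limit is one normative SD on each tool's own analysis metric: 15 for standard scores, 1.0 for z-scores, and the SD in the test manual for any scaled score. Alternatively, add a sentence to 'Data processing and analysis' that converts all six tools to one common metric with SD 15 before the limit is applied. Either change should be made before the data are analysed.

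The cost is a sentence of wording, with no change to recruitment, testing or sample size. The small downside is that TOH and SOPT can now fail. With equal SDs they would need a correlation of about 0.87 between administrations, the same demand that the printed limit already makes of a tool on the SD-15 metric.

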### Recruitment

Convenience sampling using a snowball recruitment strategy will be adopted to obtain final samples of 80 typically developing children and 40 children with cerebral palsy, including 20 who use switch access and 20 who use eye gaze technology. Community awareness will be generated through flyers and correspondence with churches, sports clubs, independent/catholic schools, the Home Education Association and the NSW/ACT Cerebral Palsy Register. Personal communication with Cerebral Palsy Alliance staff, community links and campaigns on social media moderated by Cerebral Palsy Alliance will also be used for recruitment.

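### Hypotheses 2-1 to 2-3 count a non-significant result as support for comparability, with no margin and no power statement; the problem is greatest for switch versus eye-gaze at 20 per group

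*Protocol article*

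**What the plan says.** All three hypotheses stand in the protocol article under *Primary aims and hypotheses*, Aim 2.

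- **Hypothesis 2-1** compares typically developing children with children with cerebral palsy and expects that differences "in the nomothetic span of test scores computed as within-group bivariate correlation matrices, will not be statistically significant".
- **Hypothesis 2-2**, within the cerebral palsy group, expects that "the access method (switch, eye-gaze) will not result in significant differences in the nomothetic spans of test scores".
- **Hypothesis 2-3**, also within that group, expects that "access method (switch, eye-gaze) will not have a significant effect on user experience as indicated by personal ratings of task difficulty and satisfaction".

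*Recruitment* gives the target for the cerebral palsy group as "40 children with cerebral palsy, including 20 who use switch access and 20 who use eye gaze technology", alongside 80 typically developing children. *Sample size calculations* counts 38 children with cerebral palsy.

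*Data processing and analysis* compares the correlation matrices "to examine the nomothetic spans of instruments by comparing coefficients using" Fisher's r-to-z transformation, and compares the two user-experience measures by regression. The multiplicity adjustment in that section is attached to the paired comparisons of standard with accommodated administration.

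*Sample size calculations* gives 80% power at 5% overall, an acceptable difference of 1.25 SD and an assumed true difference of up to 0.4 SD. All of these refer to standard versus modified administration. No margin, detectable difference or power is stated for Aim 2.

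**The concern.** A non-significant test shows that the data are compatible with no difference. It does not show that the difference is small, and the smaller the sample, the easier the result is to obtain. The authors use an equivalence framework with a margin for Aim 1. For Aim 2 the only criterion is the absence of significance.

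Aim 2 matters because the *Discussion* says that standard administration is not feasible for the children with cerebral palsy. In that group, the way the accommodated scores relate to one another, across groups and across access methods, is a central part of the validity evidence. If the three hypotheses are judged as worded, the study could report that switch and eye-gaze give the same construct relations and the same user experience when the data could not have shown otherwise.

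**Working it through.** **The plan's own figure.** The 80% power cannot be fully reproduced: a paired calculation needs the SD of the paired differences, which is not given. Nothing here shows it to be wrong. It concerns the equivalence of administration methods, so it does not carry over to Aim 2.

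**Inputs.** Group sizes are 20 v 20 for Hypotheses 2-2 and 2-3, and 80 v 40 (or 38) for Hypothesis 2-1. Six tests give 6 × 5 / 2 = 15 correlations per matrix. Assumptions that the article does not state: two-sided 5% per test, and illustrative true differences, with r = 0.7 v 0.3, 0.6 v 0.2 or 0.5 v 0 taken as large, 0.6 v 0.3 as smaller, d = 0.8 as large and d = 0.5 as moderate.

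**Formula for one pair of correlations.** With z = atanh(r), SE = √(1/(n₁−3) + 1/(n₂−3)). The chance of missing a true difference Δz is approximately Φ(1.96 − Δz/SE).

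**Hypothesis 2-2, 20 v 20.** SE = √(1/17 + 1/17) = 0.343.

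- 0.7 v 0.3: Δz = 0.867 − 0.310 = 0.558; Δz/SE = 1.63; missed about 63%.
- 0.6 v 0.2: Δz = 0.693 − 0.203 = 0.490; Δz/SE = 1.43; missed about 70%.
- 80% power needs Δz = (1.96 + 0.842) × 0.343 = 0.96, for example r = 0.75 v 0.
- With 18 per group after 10% dropout, SE = √(2/15) = 0.365, and the first two figures become about 67% and 73%.

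**Hypothesis 2-1, 80 v 40.** SE = √(1/77 + 1/37) = 0.200.

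- 0.7 v 0.3: Δz/SE = 2.79; missed about 20%.
- 0.5 v 0: Δz/SE = 2.75; missed about 22%.
- 0.6 v 0.2: Δz/SE = 2.45; missed about 31%.
- 0.6 v 0.3: Δz = 0.384; Δz/SE = 1.92; missed about 52%.
- With 38 in place of 40, each figure rises by one or two percentage points.

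**Hypothesis 2-3, 20 v 20.** A two-sample t-test (noncentral t, 38 degrees of freedom) stands in for the planned regression.

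- d = 0.5: power 34%, missed 66%.
- d = 0.8: power 69%, missed 31%.
- 80% power needs d = 0.91.

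**The 15 pairs taken together.** If one significant pair is enough to count against comparability, 15 independent tests at 5% give 1 − 0.95¹⁵ = 54% false rejections. Correlations among the same six scores are not independent. Simulation (20,000 runs, six scores with a common correlation of 0.5 or 0.3 in both groups, 20 v 20) gives 44–49%. Under the same rule, a difference of 0.7 v 0.3 in every pair at 20 v 20 gives at least one significant pair in about 95% of studies (59% with Bonferroni), although on average about 9 of the 15 pairs remain non-significant.

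**What an estimate would show.** At 20 v 20 the 95% half-width for a Fisher z difference is 1.96 × 0.343 = 0.67. For a mean rating it is 2.02 × √(2/20) = 0.64 SD. Intervals this wide show directly how little can be excluded.

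**The case against.** Several counter-arguments stand.

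- **Not every comparison is weak.** A reader might infer that large differences would usually pass as comparable throughout Aim 2. The figures do not support that. The 20 v 20 comparison applies only to Hypotheses 2-2 and 2-3. For Hypothesis 2-1, large single-pair differences are detected about 69–80% of the time unadjusted. For Hypothesis 2-3, d = 0.8 is detected about 69% of the time.
- **The 15 pairs do not by themselves favour a finding of sameness.** Unadjusted, with any significant pair counting, they push towards false differences and would usually flag a widespread large one. They hide differences only if each pair is read alone or a strict adjustment is used.
- **Missing multiplicity control is not an error here.** A decision rule or adjusted level for the r-to-z comparisons may stand in an analysis plan that is not shown, and an article may leave it there. Preferring an omnibus test to pairwise comparisons is a choice of method.
- **The plan is not only p-values.** Aim 2 is introduced as descriptive and comparative, descriptive statistics are planned, and regression yields estimates. The article claims 80% power only for administration methods.

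None of this removes the central point. The criterion for the three hypotheses is printed in the article under the primary aims, and an analysis plan that follows it inherits the fault.

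**Conclusion.** The point holds in a limited form. Hypotheses 2-1 to 2-3 treat failure to reject as support for comparability, without a margin and without a power statement. This is a stated rule that misleads, not omitted detail.

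The size differs by hypothesis. It is greatest for Hypothesis 2-2, where a large difference in a single correlation is missed about 63–70% of the time. For Hypothesis 2-3, moderate differences are usually missed and large ones in about three studies in ten. For Hypothesis 2-1, large single-pair differences are mostly found, but 0.6 v 0.3 is missed in about half of studies. Because the any-significant-pair reading would reject true comparability in about 44–54% of studies, unadjusted pairwise results give no reliable verdict in either direction.

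The figures rest on two-sided 5% per test, full recruitment, the illustrative effect sizes above and, for Hypothesis 2-3, a t-test approximation to the regression. The Aim 1 agreement criteria and the stated 80% power are not affected.

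**What to change.** Reword Hypotheses 2-1 to 2-3 as estimation. Report each correlation difference and each user-experience difference with its 95% confidence interval, and state that p > 0.05 will not be taken to show that there is no difference. State that Hypotheses 2-2 and 2-3 are descriptive because 20 children per group cannot establish comparability. For Hypothesis 2-1, a single omnibus comparison of the two correlation matrices is an option, not a requirement.

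The cost is wording and a little extra analysis, with no additional children. The downside is a weaker claim for Aim 2.
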